#### Wellbeing

**Pain** Pain levels in the neck, lower back, hip, knee and shoulder joint will be assessed using the numerical rating scale (NRS), consisting of an 11 point interval scale labelled from 0 to 10, with 0 being no pain, and 10 being the worst pain possible
[69]. This scale was chosen because it is easy for older adults to understand, and is sensitive to change, valid and reliable
[69].

##### 

**Quality of life** The SF12 (12 Item Short-Form Health Survey) is a self-administered questionnaire used to assess quality of life, and it is frequently used as a succinct overall assessment of health
[70]. The SF12 has good internal consistency and test–retest reliability in older adults
[71]. Two summary scales will be derived, the physical and mental summary scales. They will be scored using norm based methods
[70].

##### 

**Vitality** The vitality plus scale is used to assess the perceived benefits of exercise by older adults
[72]. It is a self-administered 10 item, multi-dimensional scale, which assesses sleep, energy, aches and pains, restlessness, stiffness, cheerfulness, constipation and appetite. Constructs of vitality relevant to exercise are therefore captured in a concise, reliable, and valid instrument, which is also easy for older adults to use
[72].

### Intervention

#### Program duration, frequency and intensity

The exercise sessions will take place at outdoor areas adjacent to the facilities which are convenient to the participants. Program duration is 12 weeks, with a session frequency of 3 times per week. Session durations for the PW and the RW groups will be 20 minutes at the start of the program, increasing to 30 minutes by week 6. Participants will be advised not to change other lifestyle habits, including PA, during participation in the program. The PW and RW sessions will be at different times and/or days so that the groups are separate throughout the program. The exercise sessions will consist of a 5 minute warm up, followed by 20 mins of RW or PW at the first session, and a cool down/stretching period of 5 mins. After six weeks, the RW/PW component will increase to 30 minutes. Participants will be asked to walk at a comfortable intensity. The reason for this is that many of the participants are expected to be frail and non-exercisers. Therefore, to reach a moderate intensity may be unrealistic for them.

#### Pole walking technique to be used

The Exerstrider technique and poles will be used in the PW group. As this PW technique requires a natural gait, continuous hand grip and no arm extension, it has fewer technical requirements for older adults to learn and perform consistently, than the Nordic walking technique
[49]. The first exercise session will be used to teach the Exerstrider technique to the PW group, and as an instruction session in the RW group.

#### Group structure and supervision

The intervention programs will consist of supervised group sessions, as there is a positive association between PA maintenance and social support from instructors and group members in older adults
[73]. Sessions will be supervised by qualified recreational therapists, who are known to the participants and experienced in leading exercise groups. Both the PW and RW group instructors will receive the same instruction and information concerning the PW and RW session procedures. PW and RW group routes will be the same at each site. In addition, the PW group instructors will be trained in The Exerstrider method. The training package is a standard one developed for use in retirement facilities by the developer of Exerstriding and master trainer of the method (personal communication). Participants in the PW group will receive a free set of Exerstrider poles and training at the beginning of the program. The RW participants will be advised at the beginning of the program that they will be given the opportunity to receive poles and training in their use at the end of the program.

The trial will be monitored by the study leader, who will visit each of the PW and RW groups once weekly to ensure compliance with study protocols. In the case of adverse events, instructors will contact facility medical staff who will arrange for onsite first aid or other intervention as appropriate. The medical staff will inform the study leader within 12 hours. The study leader will register adverse events with the University of Queensland ethics committee within 48 hours.

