### Outcome measures

Outcome measures will be assessed before commencing the program and at a follow-up testing session one week after the end of the program. The primary outcome measures are selected physical function items of the Seniors Fitness Test (30 second chair stand, 30 second arm curl, timed up and go test, and 6 minute walk test) and grip strength
[54]. Secondary outcome measures are behaviour (PA levels and sitting time), and wellbeing (joint pain, quality of life, vitality).

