### Secondary outcome measures

#### Behaviour

**Objectively measured PA and sitting time** A tri-axial accelerometer (ActiGraph GT3X+) will be used to assess levels of physical activity and sedentary behaviour in all participants in both the PW and the RW groups before, during (week 6), and at the end of the program (week 12). Participants will be shown by the lead researcher how to position the actigraph accelerometer, which will be worn on an elastic clip-on belt, above the left iliac crest. Participants will be asked to put it on when they first get up in the morning and wear it until going to bed at night. In addition, participants will be asked to complete an activity diary to verify the time that the accelerometer was worn. Valid wear time will be defined as a minimum wear time of 10 hours per day for 4 days
[62,63]. Sedentary behaviour will be defined as < 200 cpm, light intensity activity as 200–2689 cpm, moderate intensity activity as 2690–6166 cpm, and vigorous intensity activity as > 6167 cpm
[64,65].

##### 

**Self reported PA** The Active Australia Survey is a self-administered survey which is widely used to assess PA in Australian national and state surveys, and intervention studies
[66]. Items have acceptable measurement properties for ambulatory older adults
[67]. It consists of a set of questions which assess frequency and total time spent walking, and in moderate and vigorous leisure time activity in the past week. Time in each activity is multiplied by a generic metabolic equivalent value of 3.33 METs for walking and moderate activity, and 6.66 METs for vigorous activity, and the sum of all MET.minutes per week is categorized as no PA, (< 33), some PA (33–499), or meeting PA guidelines (≥ 500-999), or high PA (≥ 1000).

##### 

**Self-reported sitting time** Sitting time will be assessed by a five domain sitting questionnaire
[68]. The questionnaire assesses the number of hours spent sitting at work, while travelling, watching television, and using a computer when not at work, and during other recreation. These domain specific questions have acceptable reliability and validity
[68].

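### The offer of poles to the regular-walking group falls at program end, a week before follow-up testing, and nothing in the text holds it back until testing is done

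*Protocol article*

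**What the plan says.** Under Group structure and supervision, the protocol article states that RW participants are told at the outset that "they will be given the opportunity to receive poles and training in their use at the end of the program". The pole-walking (PW) group receives its poles and training at the start.

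Under Outcome measures, follow-up takes place "at a follow-up testing session one week after the end of the program". The primary outcomes are assessed there: "The primary outcome measures are selected physical function items of the Seniors Fitness Test", together with grip strength. The general timing statement in that section also covers the secondary outcomes. Among these, the activity survey described under Behaviour covers walking and time "in moderate and vigorous leisure time activity in the past week".

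The accelerometer has its own schedule: "before, during (week 6), and at the end of the program (week 12").

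Under Program duration, frequency and intensity: "Program duration is 12 weeks, with a session frequency of 3 times per week". The two arms meet at different times "so that the groups are separate throughout the program", and "Participants will be advised not to change other lifestyle habits, including PA, during participation in the program".

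**The concern.** The offer to the comparator and the follow-up assessment are timed from the same point. The offer is placed at that point and the assessment one week after it. Followed literally, an RW participant could be given poles, taught the technique and use it before being tested.

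PW against RW is the only comparison in the trial, so pole use in the RW arm before measurement erodes the contrast under test. If poles act on RW participants as they are hoped to act on PW participants, the observed difference shrinks.

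The analyses described under Data analysis would not remove this. The intention-to-treat set keeps everyone with baseline and follow-up data. The per-protocol set keeps everyone who completed the program. An RW participant who takes up poles after the last session belongs to both.

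**Working it through.** **Step 1: What does the end of the program mean in this document?** The accelerometer schedule puts week 12 in brackets after the phrase, and the stated program length is 12 weeks. Outcome measures then counts one week forward to testing. So the end of the program is week 12, and testing falls at 12 + 1 = about week 13.

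**Step 2: Is anything said that protects the intervening week?**
- Separation of the groups is stated for the duration of the program.
- The advice not to change activity is stated for participation in the program.
- The study leader's weekly visits are to the PW and RW groups, whose scheduled sessions have ended by then.

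None of these reaches past week 12, and no section shown makes the pole offer conditional on completed testing.

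**Step 3: Which outcomes fall after the possible exposure?**
- Exposed: chair stand, arm curl, timed up and go, 6-minute walk, grip strength, and the questionnaires taken at follow-up. For the activity survey, the one-week recall period coincides with the gap.
- Largely spared: accelerometer-measured activity and sedentary time, which are scheduled at week 12.

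**Step 4: How large is the exposure?** Program sessions: 12 weeks x 3 = 36. Gap at the same frequency: 1 week x 3 = 3 sessions. The ratio is 3/36 = 1/12, or 1 week in 13 if the gap is added to the denominator. The PW program spends its first session on teaching. If RW training did the same, about 3 - 1 = 2 practice sessions would remain.

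**Step 5: What might that do to power? (Illustration only.)** The inputs come from Sample size and Randomization: arm-curl mean 17, SD 4.1, power 0.80, significance 0.05 (taken as two-sided), and about 30 per group. The plan's own figure is reproduced first, with n = 2(1.96 + 0.84)² x SD² / Δ²:
- Δ = 20% of 17 = 3.4 gives n = 23 per group, the stated figure.
- The printed difference of 3 gives n = 30 per group.

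Now assume that the RW exposure closes 1/13 to 1/12 of the difference. The document gives no such fraction; this one simply takes the effect as proportional to time. Power by the normal approximation:

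| Δ without exposure | Δ diluted | Power at 23 per group | Power at 30 per group |
|---|---|---|---|
| 3.4 | 3.14 to 3.12 | 80% to 73–74% | about 90% to 84% |
| 3.0 | 2.77 to 2.75 | 70% to 62–63% | 81% to 74% |

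This supposes that every RW participant takes up the offer at once, so on the proportional assumption it is an upper end.

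**The case against.** The strongest reply is that this is an ambiguity and not a scheduled event. The sentence about poles reports what RW participants are told. It gives no delivery date, and a courtesy offer to a comparator arm is naturally understood as coming once the trial is over. The study-design figure, which is not shown, may make the order plain. This stands in part: the document does not show that the sponsor intends to hand out poles before testing. But the loose reading sits badly with the document's own use of the phrase for week 12, a week before testing. This is also more than an omitted detail, because a time is stated and it is the wrong side of the assessment.

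Three stronger readings are tempting, and the document does not support them.

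- *A reader might infer a measurable inflation of RW self-reported activity*, by multiplying a 30-minute pole session by the survey's 3.33 METs. That requires each pole session to be wholly additional activity. The survey gives walking and moderate activity the same 3.33 weight, so replacing a walk with a pole walk of equal length leaves the score unchanged. No RW pole sessions are scheduled in that week, and the recall period follows the supervised program in both arms.
- *A reader might infer a threat to assessor blinding*, because RW participants could mention their new poles. PW participants have had poles for 12 weeks and could mention them anyway. If both arms had poles, a remark about them would reveal less about allocation.
- *A reader might infer that the primary comparison is seriously compromised.* About 3 sessions against 36 does not support that. At 30 per group and a difference of 3.4, even the illustrative dilution leaves power at about 84%, above the 80% target. That reassurance depends on using 3.4 and not the printed 3.

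**Conclusion.** The point holds as a matter of timing. By its own definitions, the text allows RW participants to be trained in and use poles for up to one week before the physical function tests, grip strength and questionnaires. It permits this order; it does not prescribe it.

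The effect is probably small. The direction towards no difference rests on the assumption that poles affect RW participants as they would PW participants. The size cannot be derived from the document, and the power figures above illustrate an assumed proportional dilution. The past-week activity survey is the outcome whose window is most fully exposed, but no numerical bias can be assigned to it. The accelerometer outcomes at week 12 are largely unaffected.

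This is not a fatal flaw. It is an avoidable weakness in the only comparison the trial makes, and worth correcting because correction is nearly free.

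**What to change.** Under Group structure and supervision, change the timing of the offer so that RW participants receive poles and training *after completion of the follow-up testing session*, meaning once all post-program measures, questionnaires included, have been collected. Tell participants the same thing at the start.

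The cost is one phrase and a wait of about one more week for RW participants. The offer is kept, the sample size is unchanged, and no visit or staff time is added.

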#### Attendance and dropout

Attendance will be registered at each session by the session supervisor. Participants who do not attend a session will be contacted following the session by the group exercise instructor, and the reasons for their absence will be recorded. If participants indicate that they intend to discontinue the program, the reasons for this will also be recorded, and they will be encouraged to attend the post intervention assessments. If this does not occur, a last measure carried forward protocol will be used.

#### Data analysis

To ensure that randomization resulted in equal distribution of sample characteristics in both intervention groups, baseline characteristics in the intervention and control groups will be compared using t-tests for normally distributed continuous data, appropriate non-parametric tests for non-normally distributed continuous data and chi square tests for categorical variables. Between group differences in study outcomes will be examined using repeated measures of covariance (ANCOVA), adjusted for variables that are associated with both the explanatory and outcome measures; based on previous publications, these may include factors such as age, sex and number of medical conditions.

Both intention to treat analysis, including all participants who were enrolled in the study, and provided both baseline and follow up data, and per protocol analyses, including only participants who completed the program, will be analysed. The level of significance will be set at 0.05. All analyses will be conducted using SPSS version 20 (SPSS Inc, Chicago, IL).

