### Sample size

There are no previous data on the effects of PW compared with RW on physical function and psychosocial health. Sample size estimates were therefore based on the premise that the PW group would achieve changes at least 20% greater than those observed in the RW group, in selected measures of the Seniors Fitness Test (30-second chair-stand test, 30-second arm-curl test, timed up and go test, and a 6-minute walk test)
[54]. This difference is thought to be a clinically relevant difference in functional status
[52]. Of those subtests, the largest number of participants needed for a stastistically significant 20% difference was for the arm curl test. Based on a 20% difference in normative data for women aged 65–69 years for the arm curl test (mean, 17, SD, 4.1), a power of 0.80 and significance of 0.05, and using the formula n = 2[z*s^2^/Δ^2^], we estimate that 23 participants per group would be needed to detect a between group difference of 20% (i.e. mean, 3, SD, 4.1) in the change score
[52].

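### The covariate rule selects on chance association with the randomised arm, and the primary model reads as a change-score test that does not name the outcome's baseline value as a covariate: valid, but less efficient than it could be

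*Protocol article*

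**What the plan says.** All of this is in the protocol article.

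- **Model (Data analysis):** "Between group differences in study outcomes will be examined using repeated measures of covariance (ANCOVA"). The abbreviation list expands ANCOVA in the same way.
- **Covariates (Data analysis):** the model is "adjusted for variables that are associated with both the explanatory and outcome measures". Referring to earlier publications, the text adds that "these may include factors such as age, sex and number of medical conditions". Neither the outcome's own baseline value nor site is named.
- **Baseline comparisons (Data analysis):** t-tests, non-parametric tests and chi-square tests between arms are planned, with the purpose "To ensure that randomization resulted in equal distribution of sample characteristics in both intervention groups".
- **Timing (Outcome measures section):** two assessments are planned: "Outcome measures will be assessed before commencing the program and at a follow-up testing session one week after the end of the program". For one secondary outcome, the accelerometer is worn "before, during (week 6), and at the end of the program (week 12").
- **Allocation (Randomization):** 1:1 by random number generator, separately at each of four sites, about 30 per arm.
- **Sizing (Sample size):** based on a between-group difference in the change score, with the "arm curl test (mean, 17, SD, 4.1") and "a power of 0.80 and significance of 0.05", giving 23 per group.

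**The concern.** Requiring association with both exposure and outcome is how confounders are chosen in observational work. Here the exposure is the allocated arm, and nothing measured at baseline can be associated with it except through the random draw. Earlier publications can show what predicts the outcome. They cannot show what is associated with this trial's allocation. Taken literally, the rule drops a strong predictor that happens to be balanced, although adjusting for it would improve precision, and whether any adjustment is made depends on the draw.

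The second part is the model. A primary outcome measured once before and once after has only one possible repeated factor, baseline versus follow-up. The group-by-time test is then a comparison of change scores. The outcome's baseline, usually its best single predictor, enters as a response and not as a covariate. In a trial of about 60 people, precision that needs no extra data is worth taking.

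**Working it through.** **1. The plan's own figure.** Inputs from Sample size: mean 17, SD 4.1, power 0.80, alpha 0.05 (two-sided assumed).

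- Difference: 20% of 17 = 3.4.
- n per group = 2[(1.960 + 0.842) × 4.1 / 3.4]² = 22.83, so 23. The stated figure reproduces.
- The printed rounded difference of 3 would give 29.32, so 30. The 23 therefore rests on 3.4.

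**2. Change score against baseline-adjusted ANCOVA.** Let r be the correlation between baseline and follow-up, with equal variance s² at both times. Per-participant variances are:

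- change score: 2(1 − r)s²
- ANCOVA on baseline: (1 − r²)s²
- ratio: (1 − r²) / [2(1 − r)] = (1 + r)/2

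The documents do not give r, so a range is assumed. The change-score SD is held at 4.1, as the sample size section uses it. Power is by normal approximation.

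| r | Variance ratio | n per group, difference 3.4 | Power at 23 per group, difference 3.4 | Power at 30 per group, difference 3.0 |
|---|---|---|---|---|
| change score | 1 | 23 | 0.803 | 0.809 |
| 0.5 | 0.75 | 18 | 0.901 | 0.905 |
| 0.7 | 0.85 | 20 | 0.862 | 0.867 |
| 0.8 | 0.90 | 21 | 0.842 | 0.848 |
| 0.9 | 0.95 | 22 | 0.823 | 0.828 |

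For example, at r = 0.5: 22.83 × 0.75 = 17.1, so 18.

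**3. The covariate rule.** With three independent candidates, the chance that at least one differs between arms at p < 0.05 under correct randomisation is 1 − 0.95³ = 0.143.

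The rule was simulated with 30 per arm, three candidates, selection when p < 0.05 for both arm and outcome, a true effect of 0 or 0.5 SD, and 3,000 runs per setting. These settings are assumptions, because the protocol gives no threshold for association.

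- A covariate was selected in about 3% to 11% of trials.
- Type I error under the rule was 0.040 to 0.051.
- With a true effect of 0.5, the mean estimate under the rule was 0.489 to 0.500, against 0.491 to 0.504 without covariates. The rule lowered it by at most 0.006.

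Power at a true effect of 0.5 SD and r = 0.5:

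| Analysis | No covariates | Rule | Fixed set of three |
|---|---|---|---|
| Change score, strong covariates (joint R 0.6) | 0.478 | 0.475 | 0.583 |
| ANCOVA on baseline, strong covariates | 0.595 | 0.596 | 0.758 |
| Change score, weak covariates (0.3) | 0.465 | 0.464 | 0.480 |
| ANCOVA on baseline, weak covariates | 0.587 | 0.584 | 0.598 |

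The rule gives no gain in power in any row. In the first row the mean reported standard error was 0.2565 without covariates, 0.2561 under the rule and 0.2248 with the fixed set. The actual sampling variance does fall a little under the rule, (0.2500/0.2578)² = 0.94, against (0.2246/0.2578)² = 0.76 for the fixed set. The reported standard error does not reflect that fall, which fits a type I error at or slightly below 5%.

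**The case against.** **The model is inferred from a garbled name.** No sentence says that baseline enters as a repeated measure. For the accelerometer, with a week 6 and a week 12 reading, repeated measures has a natural meaning even with baseline as a covariate. This stands as a limit on certainty. For the primary outcomes, the single follow-up and the sizing on change make the pre/post reading the most natural one, and if follow-up adjusted for baseline was meant, the wording should say so.

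**A change-score analysis is legitimate.** It is unbiased after randomisation. If 4.1 is the SD of change, 23 per group already gives 80% power for 3.4, and 30 per group gives 0.895. No planned power is lost, and the point is one of efficiency.

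**The gain may be small.** A value of 0.5 for r follows only if 4.1 is both the cross-sectional and the change SD, which is not evidence about the correlation. The nearest figure is the test-retest reliability in the Senior fitness test section, 0.81 to 0.98. That is not a 12-week correlation, but at 0.98 the ratio would be 0.99.

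**The final covariate list may sit in an analysis plan that is not shown.** This is fair for the list, and an open list is not itself the defect. It does not answer the rule, which the article states and which has no valid target in a randomised comparison.

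**Stronger readings to avoid.** A reader might infer that the between-group main effect, averaged over both times, will be tested, which would halve the effect. The sample size section frames the contrast as change, and nothing supports the other reading. A reader might also infer that covariates will be picked from the baseline significance tests. The two sentences are adjacent, but the protocol attaches no action to those tests.

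**Conclusion.** The point holds as a matter of efficiency and of a badly fixed rule.

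- **Covariate rule.** It is stated outright and does not suit a randomised comparison. In simulation it forgoes nearly all the power that fixed adjustment would give: 0.475 against 0.583 for the change score with strong covariates, and little difference when covariates are weak. It is not shown to bias the estimate materially or to inflate type I error.
- **Model.** On its most natural reading it is a valid change-score test. Baseline-adjusted ANCOVA would cut its variance by 25%, 15%, 10% or 5% at r of 0.5, 0.7, 0.8 or 0.9. These values are assumed, and the formula assumes equal variances at the two times. Confidence is lower here because the wording is unclear.
- **Baseline tests.** They cannot ensure that randomisation balanced the arms. No effect on the treatment estimate follows from the text, so this is a reporting matter.

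The change is worth making, but the trial's validity does not depend on it.

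**What to change.** 1. Delete the requirement that covariates be associated with the explanatory measure.
2. For each primary outcome, specify ANCOVA of the follow-up score on arm, with that outcome's baseline value, site (allocation is done separately by site) and a small set such as age and sex, all named before the data are seen.
3. For accelerometer outcomes, specify a repeated-measures model with weeks 6 and 12 as responses and baseline as a covariate.
4. Replace the garbled model name in the Data analysis section and the abbreviation list.
5. Present baseline characteristics descriptively, without significance tests.

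No extra data collection should be needed: outcome baselines, site and age are collected under the protocol, and sex is already a named candidate covariate. With four sites, the set uses 1 (baseline) + 3 (site) + 1 (age) + 1 (sex) = 6 degrees of freedom. With 60 participants the residual falls from 58 to 52.

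### Dropouts without a post-test are imputed by one rule and excluded by another, and the set called intention to treat is a complete-case set

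*Protocol article*

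**What the plan says.** Three parts of the protocol article bear on this.

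- **Attendance and dropout.** Of participants who intend to discontinue, the article says "they will be encouraged to attend the post intervention assessments". It continues: "If this does not occur, a last measure carried forward protocol will be used".
- **Data analysis.** Two analyses are planned. One is an "intention to treat analysis, including all participants who were enrolled in the study, and provided both baseline and follow up data". The other is "per protocol analyses, including only participants who completed the program". Carried-forward values are not mentioned here.
- **Outcome measures.** The article sets the schedule thus: "Outcome measures will be assessed before commencing the program and at a follow-up testing session one week after the end of the program". Only one measure has an intermediate time point: the accelerometer (week 6, under Behaviour), which is a secondary outcome. Every primary outcome, meaning the four Seniors Fitness Test items and grip strength, has one baseline and one follow-up value.

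**The concern.** Both rules are current text and both apply to the same people: those who stop the program and do not return for the post-test. One gives them a value and the other removes them. Per protocol is limited to completers, so read literally the carried-forward values enter neither analysis. An analyst could settle the matter either way after seeing the data.

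Two further problems follow. First, a set that requires follow-up data is a complete-case set. A reader who sees it called intention to treat will assume that everyone randomised was analysed. Second, with a single post-baseline visit the last measure is the baseline. Carrying it forward states that the dropout did not change at all, and treats that value as observed. Both arms exercise for 12 weeks and the Sample size section expects changes in both, so zero is not a neutral value. If the arms lose different proportions of people, the imputed zeros move the comparison.

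**Working it through.** **Inputs from the article.** Arm curl mean 17 and SD 4.1, a 20% difference, "a power of 0.80 and significance of 0.05", 23 per group required (Sample size); about 30 per group planned (Randomization). The article gives no dropout rate, no expected gain in the walking arm and no pre-post correlation. Values for these below are assumptions. Two-sided testing is also assumed.

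**The article's own figure.** 20% of 17 is 3.4. Then n = 2 × (1.96 + 0.84)² × 4.1² / 3.4² ≈ 22.8, so 23 per group, as stated. The working below uses 3.4 because that value reproduces 23. The printed, rounded difference of 3 would give 30 two-sided. The contradiction does not depend on this figure.

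**The two rules side by side.** With 60 randomised and an assumed 20% without a post-test, carrying forward analyses 60 people. The set in Data analysis keeps 60 × 0.80 = 48.

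**What carry-forward estimates.** Let g be the mean change and d the dropout proportion in each arm. If dropouts would have changed as much as completers, the expected difference is

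(1 − d_PW) × g_PW − (1 − d_RW) × g_RW.

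*Equal dropout, true difference 3.4.* This reduces to (1 − d) × 3.4. Power is at 30 randomised per arm with change-score SD 4.1. The carry-forward range is for a mean RW change of 2 or 0.

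| Dropout per arm | Complete cases per arm | Power, complete case | Carry-forward difference | Power, carry-forward |
|---|---|---|---|---|
| 10% | 27 | 0.86 | 3.06 | 0.83–0.85 |
| 20% | 24 | 0.82 | 2.72 | 0.75–0.79 |
| 30% | 21 | 0.77 | 2.38 | 0.66–0.73 |

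*No true difference, both arms gaining g.* The formula becomes g × (d_RW − d_PW). With g = 2:

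- PW 20%, RW 10%: 2 × (0.10 − 0.20) = −0.2 curls.
- PW 30%, RW 10%: 2 × (0.10 − 0.30) = −0.4 curls.

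The sign reverses if RW loses more people.

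**Type I error by simulation** (30 per arm, SD 4.1, 8,000 trials per scenario, nominal 5%):

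| Dropout PW / RW | Gain in both arms | Correlation | Carry-forward bias | Carry-forward type I error |
|---|---|---|---|---|
| 20% / 20% | 2 | 0.7 | 0 | about 5% |
| 20% / 10% | 2 | 0.7 | −0.2 | about 6% |
| 30% / 10% | 1 | 0.7 | −0.2 | about 6% |
| 30% / 10% | 2 | 0.5 | −0.4 | about 7% |
| 30% / 10% | 2 | 0.7 | −0.4 | about 9% |

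Correlation matters because the change-score SD is 4.1 × √(2 × (1 − r)): 4.1 at r = 0.5, which matches the SD that Sample size attaches to the change score, and about 3.2 at r = 0.7. In the same scenarios, complete-case ANCOVA adjusted for baseline gave a mean difference of about 0 and a type I error of about 5%. Missingness there depended on arm only.

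**The case against.** The strongest reply is that the set described in Data analysis, though mislabelled, need not mislead. If missingness depends only on arm and the adjusted covariates, a complete-case ANCOVA is unbiased, and the simulation bears this out. This stands. A reader might infer that neither written rule can give a sound result, but the documents do not support that. The quantified harm belongs to the carry-forward rule. The fault in the other rule is its label and its unstated assumption.

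Second, the shrinkage of a true difference is a bias only if dropouts would have gained what completers gained. People who stop the program may gain little. The carry-forward figure could then lie close to the effect of assignment, which is what intention to treat targets. The same caveat applies to the −0.2 and −0.4. This also stands, and it is why these figures are conditional.

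Third, the 9% is the top of the range examined. It needs a threefold imbalance in dropout, a 2-curl gain and a correlation of 0.7, none of which the article gives. At 20% versus 10% the excess is about one percentage point, and at equal dropout there is none. It should not be read as the trial's expected error rate.

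Fourth, reporting intention-to-treat and per-protocol results together is ordinary, and the details of imputation may sit in a statistical analysis plan that is not shown. Both are fair. But the article is not silent here: it states two incompatible rules, and any later plan would have to overrule one of them. Counting a carried-forward baseline as follow-up data that the participant supplied is strained, and it would largely empty the restriction of effect.

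**Conclusion.** The contradiction is real and needs no assumption: the same participants are imputed in one section and excluded in another. The mislabelling is equally plain. For every primary outcome, carry-forward means zero change.

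The numerical consequence is conditional. With both arms gaining an assumed 2 curls and no true difference, carry-forward biases the comparison by 2 times the difference in dropout proportions, or 0.2 to 0.4 curls in the cases shown. Type I error runs from about 5% with equal dropout to about 6–9% with unequal dropout. A true difference shrinks by the dropout proportion if dropouts would have done as well as completers. Unequal dropout is plausible, since participants are unblinded and only one arm has a technique to learn, but the article gives no rate.

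This should be fixed before outcome data are analysed by arm. The evidence does not show that the trial's result would be invalid under every reading of the plan.

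**What to change.** 1. Reconcile Attendance and dropout with Data analysis so that one rule covers participants without a post-test.
2. Define intention to treat as all randomised participants in the arm assigned, and make it the primary analysis set.
3. Replace carry-forward as the primary method with one stated method valid under missing at random. Either use multiple imputation by arm (baseline value, site, age, sex, attendance) feeding a baseline-adjusted ANCOVA, or use a likelihood-based mixed model. With one follow-up visit, either will give nearly the same estimate as a complete-case ANCOVA with the same covariates. The gains are a true intention-to-treat set, a stated assumption and, with imputation, the use of attendance data.
4. Report complete-case and per-protocol results as supportive. Carry-forward may stay if wanted, labelled as a sensitivity analysis that assumes zero change in dropouts.

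The cost is a wording change and a little analysis work with standard methods. No extra visits, participants or measurements are needed.
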